# III. PRIMARY AND SECONDARY ENDPOINTS

## Primary endpoint

The primary endpoint will be the prevalence of falciparum malaria measured by qPCR, 12 months after the first administration of TCE.

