## Study populations, sample size and statistical considerations

Four villages in total per site will be identified in regions where artemisinin resistance has been documented. Each village will be of about 250-1200 people each.. Villages will be selected based on quantitative reasons (prevalence parasitaemia) and qualitative reasons (expected enthusiasm of the residents resulting in an adequate coverage). Two out of the four villages in each site will be randomized to receive TCE, the remaining two will receive no treatment (control villages).

The primary objective of this study is to test the feasibility and acceptability of implementing TCE in the six study areas, as well as its safety, efficacy and effectiveness in reducing asymptomatic malaria prevalence. Hence the primary analysis will be of the percentage falls in asymptomatic malaria prevalence in the TCE villages as determined by highly sensitive RT-PCR. We hope to see 95% reductions in prevalence rates in all sites at the end of one year.

To ensure that any reductions seen are not due to changes in endemicity unrelated to the TCE, we will also conduct a formal overall analysis comparing changes in prevalence in each study area between the TCE villages and non-TCE control villages. There will be a total of at least 4 villages in each area. For 80% power to detect a 95% fall in prevalence from a 10% initial prevalence (controlled for random changes in prevalence in the control groups) there will be a minimum required participants to be recruited and followed up of at least 152 individuals in each village. Analysis will be as a cluster randomised, repeated measures RCT, using a hierarchical logistical regression model accounting for between area (country), between cluster and between individual effects.

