### 1.2 First exhaustive cross-sectional surveys and first TCE round

Exhaustive cross sectional surveys will be carried out in the selected villages (4 per site). Depending on the village size and level of participation, a total of about 3 days per village will be needed to conduct the first TCE round and associated survey. Individual informed consent will be asked from all participants or their attending relatives in individuals under 18 years of age (or lower depending on local guidelines). The samples (3 mL for participants 5.0 years and older, 0.5mls for those below 5 years) will be used for parasite DNA detection and gametocyte RNA assessment in those with >1000 copies/µL.

For each participant, in the TCE villages, blood sampling will be followed by a full treatment course of DP (total treatment of 3 days) plus PQ 0.25 mg/kg single dose. We will use the census data to follow-up and treat at home people who miss rounds of treatment; we will also follow-up at home any residents who miss cross-sectional surveys so that we can collect samples. When participants miss treatment or surveys due to being out of the village, messages will be left at home. Participants will be identified by biometrics (e.g. fingerprint or iris recognition), which will be linked to a unique identifier and barcode. Identification methods will be discussed per village. Possibilities include that individuals will receive a notebook (1 per family), a carton card or a bracelet with the barcode which can be used for later identification. All houses will be geo-localized by GPS.

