### 2.1 Cross sectional surveys

Cross sectional surveys will be conducted on the entire village population who consent to be surveyed (including those not enrolled initially for TCE) starting with the first TCE round, then one month after the final round of TCE and thereafter at 3 month intervals. The approximate timing of the cross sectional surveys will be:

- First survey with TCE first round (month 0)
- First post-TCE (month 3)
- Post-TCE month 6
- Post-TCE month 9
- Post-TCE month 12 (1 year)

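### The pooled TCE-versus-control comparison is worded as a difference in changes; using month 0 as a baseline adjustment would usually give a narrower interval at almost no cost

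*Protocol*

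**What the plan says.** Under Study populations, sample size and statistical considerations, the protocol describes two analyses. The first is the percentage fall within TCE villages, which has no control arm. The second is the randomised comparison: "we will also conduct a formal overall analysis comparing changes in prevalence in each study area between the TCE villages and non-TCE control villages". Later in the same paragraph it names the method, a repeated-measures analysis that respects the village clusters. The model is described in these words: "using a hierarchical logistical regression model accounting for between area (country), between cluster and between individual effects". It does not say which time, treatment and baseline terms this model contains, and it names no adjustment for month 0 prevalence.

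The primary endpoint is a level and not a change: "prevalence of falciparum malaria measured by qPCR, 12 months after the first administration of TCE".

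Baseline data exist in every village. Sections 1.2 and 2.1 of the Procedures provide for an exhaustive survey at month 0 in all four villages of each site, two of which are randomised to TCE.

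**The concern.** A difference in changes subtracts the whole month 0 value from the month 12 value. This is efficient only when village prevalence is very stable over the year. Otherwise it brings baseline sampling error and short-term variation into the treatment effect. In an observational comparison that might be the price of removing bias. Here villages are allocated at random, so expected month 0 prevalence is equal between arms and there is no bias to remove.

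This is the only analysis in the plan that uses the randomisation, and it rests on few clusters. The stake is the width of its confidence interval and, if TCE works less well than hoped, its power.

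**Working it through.** **Inputs from the protocol.** Two TCE and two control villages per area. Four sites (16 villages) or six areas (24 villages), since the text gives both. At least 152 people per village, 10% initial prevalence, and a planned 95% fall (to 0.5%).

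**Assumptions, not in the protocol.** Two-sided alpha 0.05, between-village SD 0.5 on the logit scale, and a range of month 0 to month 12 village correlations (rho).

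**The plan's own figure.** The protocol gives no number for baseline handling. Its 152 per village is used here only as a cluster size. A plain two-proportion formula for 10% against 0.5% at 80% power gives 86 per arm (106 with continuity correction), against 2 × 152 = 304 per arm in one area. The gap may be an allowance for clustering, but no such inputs are stated. The 152 therefore cannot be reproduced, and it is not shown to be wrong.

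**Step 1, large-sample formula.** With equal village variances scaled to 1:
- difference in changes: 2(1 − rho)
- adjusted for month 0: 1 − rho²
- width ratio, change to adjusted: √[2(1 − rho)/(1 − rho²)] = √[2/(1 + rho)]

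This gives 1.29, 1.15 and 1.05 at rho 0.2, 0.5 and 0.8.

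**Step 2, cost of estimating the slope.** With area as a stratum, 16 villages leave 16 − 4 − 1 = 11 degrees of freedom, or 10 with the covariate (t = 2.201 and 2.228). Estimating the slope inflates the variance by 1 + 1/(11 − 2) = 1.111. The ratio is multiplied by (2.201/2.228) × √(1/1.111) = 0.937, giving 1.21, 1.08 and 0.99. For 24 villages (17 and 16 degrees of freedom) the results are 1.24, 1.11 and 1.02.

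**Step 3, sampling error.** The rho in steps 1 and 2 is the correlation of observed prevalences, which is lower than the true one. At 10% prevalence the sampling variance of a village log-odds is 1/(152 × 0.10 × 0.90) = 0.073, against a between-village variance of 0.5² = 0.25. With no treatment effect, a true rho of 0.8 is observed as 0.8 × 0.25/0.323 = 0.62. The 16-village ratio becomes √(2/1.62) × 0.937 = 1.04, so adjustment still helps slightly.

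**Step 4, simulation** (village empirical logits, area fixed effects, 152 per village, SD 0.5, 3,000 trials per setting, true fall 50%):

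| | rho 0.2 | rho 0.5 | rho 0.8 |
|---|---|---|---|
| 16 villages: width, adjusted/change | 0.825 | 0.889 | 0.959 |
| 16 villages: power, change → adjusted | 44% → 58% | 54% → 63% | 68% → 72% |
| 24 villages: width, adjusted/change | 0.802 | 0.866 | 0.933 |
| 24 villages: power, change → adjusted | 60% → 79% | 70% → 82% | 86% → 91% |

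Type I error of the adjusted analysis was 4% to 6%. At a 95% fall the width ratio was 0.82 to 0.98 over rho 0.2 to 0.95, and power was 100% for both analyses in every setting.

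**Step 5, where the gain stops.** With 16 villages, 500 sampled per village, SD 0.8 and a 50% fall, the adjusted interval is slightly wider: ratio 1.02 at rho 0.9 and 1.03 at 0.95. Power is 86% for change against 84% adjusted at 0.9, and 96% against 94% at 0.95.

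**Step 6, four villages alone.** A covariate leaves 1 degree of freedom in place of 2 (t = 12.71 against 4.30). The change interval is then only 0.33 to 0.45 times as wide as the adjusted one on the logit scale, so adjustment by an estimated slope is clearly worse.

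**The case against.** The strongest reply is that the sentence about changes states a purpose, namely to rule out secular trends, and that the method is the repeated-measures model named afterwards. That model already uses the month 0 data. With one month 0 mean common to both arms it behaves like a baseline adjustment, and a statistical analysis plan may say so. This stands in part. A reader might infer that the protocol fixes a change-score estimator, but it does not. It does word the comparison as one of changes, which points to separate month 0 means, and nothing in the text says otherwise.

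A second reply is that the simulation uses village-level regression and not the planned individual-level hierarchical model. That also stands: the percentages indicate size and are not the exact loss in the planned model.

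A third is that nothing would change at the planned effect. On power this is right. A reader might infer from the table that the trial is underpowered as planned, but those gains are for a 50% fall. On the prevalence-difference scale the gain looks larger (change intervals 1.20 to 1.66 times as wide), but the named model is logistic, so the logit-scale figures are the relevant ones.

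**Conclusion.** The point holds as a worthwhile, low-cost improvement to the pooled analysis. It does not show an invalid one: a difference in changes is unbiased here and its type I error is not in question. With 16 to 24 villages, 152 per village and a logit SD of 0.5, month 0 adjustment narrows the interval by roughly 10% to 20% at village correlations of 0.2 to 0.5 and by about 4% to 8% at 0.8. At about 0.9 or above with larger villages there is no gain, or a loss of 2% to 3%. Power improves only for effects well below the planned 95% fall.

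The correlation, SD and alpha are assumptions, and the protocol is inconsistent on the number of areas. It would be tempting to say that adjustment is always better, or that it should also be applied to the four Lao villages described under Type of study. Neither follows: the first depends on the unknown correlation, and the second is contradicted by step 6.

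**What to change.** State that the pooled all-area hierarchical model estimates the month 12 TCE effect in one of two ways:
- with the month 0 mean constrained equal between arms within area, or
- with village month 0 log-odds as a covariate.

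In both cases area is a stratum and inference uses small-sample degrees of freedom. The common-mean version should include a village-by-survey term as well as a village term. Otherwise the model treats villages as stable apart from sampling error. Add that no village-level baseline slope is estimated from a single four-village site; the unadjusted comparison of changes can stay there.

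If a statistical analysis plan already says this, only the protocol wording needs aligning.

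The cost is a sentence or two and no new data. The covariate version uses one degree of freedom (11 to 10 with 16 villages) and may give a very slightly wider interval if villages turn out to be extremely stable.

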# IV. STUDY DESIGN

## Type of study

This is a cluster randomized, controlled, not-blinded clinical trial including residents of four Lao villages. Two villages will receive the intervention (TCE) and the other two will be the controls. The control villages will help explain non-TCE related trends in malaria prevalence over the year such as seasonal effects as well as changes in detectable falciparum over the year in the absence of treatment and on the infectivity of non-clinical parasitaemia. Five or more villages will be pre-surveyed first leading to selection of four villages per site, of which two will be randomised to TCE and two to non-TCE control. The control villages will be TCE treated the following year should TCE prove successful.

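### The model for comparing change in prevalence between TCE and control villages names no village-by-survey effect, so independent village drift is counted as person-level error and the intervals are too narrow

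*Protocol*

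**What the plan says.** The Type of study section randomises whole villages and gives the controls a purpose: "The control villages will help explain non-TCE related trends in malaria prevalence over the year". The section on study populations, sample size and statistical considerations makes the primary analysis the percentage fall in the TCE villages. It adds a formal controlled analysis, meant to rule out changes in endemicity unrelated to TCE, "comparing changes in prevalence in each study area between the TCE villages and non-TCE control villages".

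The same section fixes the method. On the type of analysis it says: "Analysis will be as a cluster randomised, repeated measures RCT". The model and its sources of variation are then given as follows: "using a hierarchical logistical regression model accounting for between area (country), between cluster and between individual effects". No village-by-survey effect is named there or elsewhere in the protocol. The power statement concerns "a 95% fall in prevalence from a 10% initial prevalence (controlled for random changes in prevalence in the control groups") and asks for "at least 152 individuals in each village". No ICC, no size for village-level change and no significance level is given.

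**The concern.** The quantity tested is a difference in change, that is, an arm-by-survey contrast. An area, village or person effect that stays the same at every survey drops out of a before-after change. A fixed survey effect absorbs only the trend that all villages share. Variation in change from one village to another, for example from local transmission or migration, is left without a term.

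For this contrast, villagers are then treated as independent although villages were allocated. The comparison is there to separate a TCE effect from other changes, yet ordinary drift between villages could itself yield a significant difference. The protocol foresees such movement, since its power statement refers to random changes in the control groups, but none of the listed components measures it.

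**Working it through.** **The plan's own figure.** The 152 per village is not clearly reproducible. For 10% falling to 0.5% with 80% power and two-sided 5%:
- two independent proportions give 86 per arm (106 with continuity correction);
- a difference in differences gives 240 per arm (120 per village) on the risk scale and 192 per arm (96 per village) on the logit scale.

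A one-sided 5% logit difference in differences with no between-village term does come close. The log-odds difference is ln(0.1/0.9) − ln(0.005/0.995) = 3.096, and the variance sum is 3/0.09 + 1/(0.005 × 0.995) = 234.3. So n = (1.645 + 0.842)² × 234.3 / 3.096² = 151.1, or 152, but per arm. A design effect of 152/86 = 1.77 (ICC about 0.005) would also give 152. The protocol does not say which was used, so 152 does not show that village-level change was allowed for.

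**Inputs for the check.** From the protocol: 10% prevalence, 152 people per village, villages of about 250-1200 people, and whole-village surveys at months 0 and 12. Assumed: ICC 0.01, 0.05 or 0.10 on the logit scale; a stable share of village variance of 1.0, 0.8 or 0.5; a two-sided 5% test; people independent between surveys; no TCE effect.

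**Formulas.**
- Village logit variance: v = ICC/(1 − ICC) × π²/3.
- Variance of a village's own change: s² = 2 × (1 − stable share) × v.
- Person-level variance of a village's logit change: e = 2/(n × 0.1 × 0.9).
- With k villages per arm, the true variance of the contrast is 2(s² + e)/k, and the listed model uses 2e/k. The ratio is 1 + s²/e, and k cancels.
- False-positive rate = 2 × [1 − Φ(1.96/√(1 + s²/e))].

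For n = 152, e = 2/13.68 = 0.146. For n = 500, e = 2/45 = 0.0444.

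| n per village | ICC | Stable share | s² | Variance ratio | Actual rate |
|---|---|---|---|---|---|
| 152 | any | 1.0 | 0 | 1.00 | 5.0% |
| 152 | 0.01 | 0.8 / 0.5 | 0.013 / 0.033 | 1.09 / 1.23 | 6.1% / 7.7% |
| 152 | 0.05 | 0.8 / 0.5 | 0.069 / 0.173 | 1.47 / 2.18 | 10.6% / 18.5% |
| 152 | 0.10 | 0.8 / 0.5 | 0.146 / 0.366 | 2.00 / 3.50 | 16.6% / 29.5% |
| 500 | 0.05 | 0.8 / 0.5 | 0.069 / 0.173 | 2.56 / 4.90 | 22.0% / 37.6% |

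**Check with fitted models.** Logistic models with village and person random intercepts, arm, survey and arm-by-survey were fitted to simulated trials (1000 per setting, n = 152, likelihood-ratio test). The protocol describes four Lao villages, four sites or six areas in different places, so 4, 16 and 24 villages were run.

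| SD of a village's logit change | 4 villages | 16 villages | 24 villages |
|---|---|---|---|
| 0 | 4.8% | 6.7% | 4.9% |
| 0.25 | 9.3% | 8.4% | 10.3% |
| 0.35 | 13.7% | 15.2% | 12.5% |
| 0.50 | 21.9% | 24.3% | 23.1% |

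The rate does not fall as villages are added. A t-test on village-level logit changes stayed at 3.6-5.5% in every cell. Correlation within persons makes matters worse: in the closed form at n = 152, a 10% rate needs a drift SD of 0.25 with no such correlation and 0.18 with a correlation of 0.5.

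**The case against.** The protocol gives one sentence and no equation. It does not say random intercepts, and between-cluster effects could be stretched to include village-specific slopes. Choosing among such terms is often left to the SAP, which is not shown. This limits how firmly the fault can be asserted. Still, the protocol did not leave the model open: it lists the effects for a repeated-measures comparison of change, and the ordinary reading of area, cluster and individual is one constant effect at each level. An SAP that follows the list inherits the fault.

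Three further limits stand. First, a reader might infer that the false-positive rate is simply two to four times nominal. The documents do not support this, because that range belongs to one assumed slice (ICC 0.05, 152 people, stable share 0.8 to 0.5). Trends shared by all villages, such as a common seasonal effect, cause no inflation. Second, a reader might infer that drift could explain the result the trial hopes for. It could not. At ICC 0.05 the SD of a village's logit change is √0.069 = 0.26 to √0.173 = 0.42, while 10% to 0.5% is 3.1 logits, roughly 7 to 12 such SDs. Nor does the protocol tie expansion to this test: it ties it to a reduction of at least 95%. Third, the calculations use two of the five whole-village surveys, so they do not describe every analysis the five surveys would allow.

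**Conclusion.** The concern holds in a conditional form. As the model is listed, the TCE-versus-control comparison of change has intervals that are too narrow whenever villages drift independently. Without village-specific drift the test keeps its level. With it, a nominal 5% test at 152 people per village runs at about 6-8%, 11-19% or 17-30% for ICC 0.01, 0.05 or 0.10, and at about 22-38% for ICC 0.05 and 500 people. Surveying more people per village worsens the inflation, and the protocol surveys all who consent.

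These figures rest on the plain reading of the effects list, on assumed ICCs and stable shares, and on a month 0 to month 12 contrast. The consequence is that a modest difference could be declared significant in the safeguard comparison. The within-TCE percentage fall is not affected.

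**What to change.** In the statistical considerations section, define the TCE effect as the arm-by-survey contrast at month 12. For the pooled multi-area analysis, add a village-by-survey random effect to the village and individual effects and base inference on village-level degrees of freedom.

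Where too few villages are analysed to estimate that variance, four for example, compare village-level changes between arms on a scale that tolerates zero counts, such as change in prevalence, stratified by area if more than one is included. A log-odds change with a 0.5 correction is not an equivalent substitute. At 0.5% and 152 people the expected count is 0.76, and 0.995^152 = 47% of TCE villages would have no infections, so the result would hang on the correction.

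The change costs wording only and needs no new data. Intervals will be wider. With two villages per arm, ICC 0.05 and 152 people, the village-level log-odds test has about 56-66% power for 10% to 0.5%, so the stated 80% should be restated if only four villages are analysed. Power was close to 100% with 8 or 12 villages per arm. The 152 should be re-justified with a stated between-village variance of change.

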## Study sites and duration

TCE will be pilot-implemented in four sites and its effects and falciparum malaria-elimination potential will be evaluated over the course of one year; there will be two TCE villages per site and two non-TCE villages which will serve as controls. The study has been implemented in two sites on the Thai-Myanmar border and Vietnam during the first year of the project . Sites in Myanmar, Laos and Bangladesh will be added in 2015.

Prior to the beginning of the pilot-implementation of TCE in the first year, all sites will be pre-surveyed for selection of the TCE and control villages: five or more candidate villages in each region will be visited prior to TCE pilot-implementation and 50 random 2 mL blood samples per village will be taken from adults to estimate the prevalence of submicroscopic infections; 4 villages will be chosen based on a dry season malaria prevalence >10% for piloting TCE implementation during the first year. All malarias will be includes independent of the Plasmodium species. In very low density infections it is often not possible to determine the species. Once chosen, the villages will be visited regularly to engage with and prepare the community. This work leading up to the main TCE implementation will be documented as it is essential to ensure that TCE coverage will be as close as 100% as possible after excluding individuals based on appropriate exclusion criteria.

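### The only controlled comparison is a hierarchical logistic model that does not fit the four-village trial as defined: large-sample inference would be unreliable with two villages per arm, and the odds ratio has no finite estimate if all TCE villages reach zero

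*Protocol*

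**What the plan says.** Protocol section IV describes the scope of the trial in three ways.

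- *Type of study*: a cluster-randomised trial "including residents of four Lao villages", and "Two villages will receive the intervention (TCE) and the other two will be the controls".
- *Study sites and duration*: "TCE will be pilot-implemented in four sites", with two TCE and two control villages per site.
- *Study populations, sample size and statistical considerations*: "implementing TCE in the six study areas", and "There will be a total of at least 4 villages in each area".

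The last of these sections calls the drop in prevalence within the TCE villages the primary analysis. It then adds an overall comparison with the control villages, to rule out changes in endemicity unrelated to TCE. That comparison is a cluster-randomised, repeated-measures analysis "using a hierarchical logistical regression model accounting for between area (country), between cluster and between individual effects". The section does not give a significance level, test statistic, reference distribution or between-village variance.

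The sample size reads "For 80% power to detect a 95% fall in prevalence from a 10% initial prevalence", with "at least 152 individuals in each village". The background section gives elimination as the goal; the numerical target is a 95% fall. The data handling section lets each site publish its own data.

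**The concern.** The primary analysis has no control group, so the hierarchical model is the only formal protection against mistaking a secular trend for an effect of TCE. Two features of the plan put that protection at risk.

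1. If the Lao villages are analysed alone, as the type-of-study text and the publication rule allow, there is one country and there are four clusters. The country effect cannot be estimated, the village variance rests on four units, and normal or chi-square reference distributions are poor approximations.
2. The better TCE works, the fewer infections remain in the treated arm. At zero infections in every TCE village the maximum-likelihood odds ratio has no finite value.

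At stake are a false claim of effect in a small single-site report and an uninformative odds ratio after complete success.

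**Working it through.** **Inputs from the protocol.** Two versus two villages; at least 152 people per village, villages of about 250 to 1200; prevalence 10% falling by 95% to 0.5%; 80% power; four sites or six areas if pooled (8 or 12 villages per arm).

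**Assumed inputs.** Two-sided 5% level; village SD of 0.25 to 0.8 on the log-odds scale; equal village sizes; no repeated-measures correlation within individuals.

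**The plan's own figure.** A two-proportion formula for 10% versus 0.5% gives 86 per arm, or 106 with continuity correction, not 152 per village. The figure can be back-fitted only with an unstated clustering input. With two clusters per arm and between-village coefficient of variation k, 2 = 1 + 7.849 × [0.094975/m + k² × 0.010025]/0.095². At m = 152 this gives k ≈ 0.23. Since k ≈ SD × (1 − 0.10), an SD of 0.25 corresponds to k ≈ 0.23, so the lowest assumed SD matches the back-fitted value.

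**Type I error, two versus two villages, month-12 data.** A village random-intercept logistic model was fitted by maximum likelihood to data with no TCE effect and 10% prevalence, 500 runs per row (simulation error about 1 to 2 points).

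| Village SD | People per village | Wald | Likelihood ratio | t-test on village log-odds (2 df) |
|---|---|---|---|---|
| 0.25 | 152 | 10% | 8% | 4% |
| 0.5 | 152 | 21% | 15% | 6% |
| 0.8 | 152 | 25% | 19% | 3% |
| 0.25 | 400 | 21% | 17% | 6% |
| 0.5 | 400 | 26% | 20% | 5% |
| 0.8 | 400 | 28% | 21% | 5% |

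The large-sample limits agree. A z reference with an unbiased variance gives P(|t₂| > 1.96) = 1 − 1.96/√(2 + 1.96²) = 19%. The maximum-likelihood Wald test gives P(|t₂| > 1.96 × √(2/4)) = 30%.

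**Month 0 plus month 12, village intercept only, one site, 152 per village.** About 4% if village time trends do not vary (400 runs); 13% and 26% if they vary with SD 0.25 and 0.5 (300 runs each).

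**Pooled over sites.** Degrees of freedom are villages − sites − 1.
- Four sites: 16 − 4 − 1 = 11 df, limits 7.6% (z, unbiased variance) to 13% (maximum-likelihood Wald). In 150 simulated runs at SD 0.5, Wald gave 13% and the village-level t-test 8%; runs of this size are too few to separate 8% from 5%.
- Six sites: 24 − 6 − 1 = 17 df, limits 6.7% to 12%.
- With trend SD 0.5 and only a village intercept, four sites still gave 28% (100 runs, error up to 4.5 points).

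**Zero infections at the 0.5% target.** The expected count is 152 × 0.005 = 0.76 per TCE village. The probability of none is:
- two villages of 152: 0.995³⁰⁴ = 22%;
- two villages of 250: 0.995⁵⁰⁰ = 8%;
- two villages of 1200: about 0;
- eight pooled villages of 152: 0.995¹²¹⁶ = 0.2%.

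**What the model returns at zero.** With 0/152 and 0/152 against 15/152 and 16/152, the fitted log odds ratio runs off to about −16 with a standard error near 500. The Wald p is 0.97, while the likelihood-ratio p is 0.002. The prevalence difference is 31/304 = 10.2 points.

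**Randomisation floor.** One site has C(4,2) = 6 allocations, so the smallest two-sided p is 2/6 = 0.33. Four sites have 6⁴ = 1296, so it is 2/1296 = 0.0015.

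**The case against.** The strongest reply is that the model was never meant for four villages. The protocol calls it an overall analysis and gives it a country term, which makes sense only across areas with 8 or 12 villages per arm. It names a model but no test, estimator or degrees of freedom. A statistical analysis plan could supply a small-sample correction, a penalty or priors. The analysis called primary is the percentage fall, which is 100% and finite at zero infections. Surveys cover all consenting residents, so 152 is a floor, and larger numbers make zero counts unlikely at the 95% target. A repeated-measures fit also holds its level if village trends are parallel.

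Most of this stands, and it rules out two stronger readings. A reader might infer that the protocol commits to an invalid test. It does not, because the inflation arises only under default large-sample inference, which is not specified. A reader might also infer that the effect cannot be estimated if TCE succeeds. Only the maximum-likelihood odds ratio and its Wald interval fail; a likelihood-ratio test, the prevalence difference and the percentage fall remain.

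The reply does not remove the contradiction in scope. The protocol defines the trial as four villages in one country, yet prescribes a model that such a trial cannot support. Pooling reduces the excess type I error without removing it, and larger villages make it worse. Parallel village trends are an assumption the protocol does not justify.

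**Conclusion.** The point holds in a conditional form. The protocol leaves open whether inference is for four Lao villages or for pooled areas, and its one controlled analysis suits only the second. For the Lao villages alone, large-sample inference on month-12 data would give about 8% to 28% type I error instead of 5%. Pooled over four to six sites the figure is about 7% to 13%, and higher if village trends vary and are not modelled. These figures rest on the assumed village SDs and on 152 to 400 people per village; 8% corresponds to the likelihood-ratio test at the lowest SD and at 152.

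The odds ratio fails with certainty if every TCE village reaches zero. At the 95% target the risk is 22% or less for two villages and negligible for eight. The primary percentage fall is unaffected, but it carries no control comparison. The change is worth making because this model is the stated safeguard against secular trends.

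**What to change.** 1. State whether inference is for the four Lao villages or pooled over sites, and reconcile the references to four villages, four sites and six areas.
2. Make the pooled between-arm comparison a village-level analysis of month-12 prevalence adjusted for month 0 and stratified by site, with a permutation test within site or small-sample degrees of freedom.
3. Report the prevalence difference. If a ratio is wanted, use a penalised (Firth-type) estimate that stays finite at zero.
4. Report a single-site result as an estimate with an interval on 2 df, for example from village changes since month 0 (four villages less two arm means), and make no significance claim.

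**Cost.** Only the analysis wording changes. The pooled village-level analysis loses some efficiency against an individual-level model. One site alone yields no confirmatory test, and its interval uses a multiplier of 4.30 in place of 1.96, about 2.2 times as wide for the same standard error. That width reflects what four villages can support.
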